## Abstract

**Introduction:**

Parents of children with a neurodevelopmental disorder (NDD) experience more stress than parents of typically developing children. In a cocreation process with experts and parents, a low-threshold application that uses exercises based on the principles of positive psychology and mindfulness was developed. This application, called “Adappt,” aims at enhancing the ability to adapt of the parents and caregivers of children with NDDs and at supporting their mental health. This protocol describes the evaluation study of the effectiveness of Adappt, its core working mechanisms and user experiences.

**Method:**

A pragmatic international multicenter randomized controlled trial will compare the effectiveness of Adappt with a (delayed) waitlist control condition. At least 212 parents or primary caregivers of children younger than 18 years diagnosed with or suspected of a NDD will be randomly assigned to the intervention or waitlist control condition. Participants are excluded if they have severe anxiety or depression levels or are in treatment for mental health issues. Measures will be collected online at baseline, post-intervention (1 month after baseline), and 4 and 7 months after baseline. The primary outcome is the improvement in generic sense of ability to adapt as measured with the Generic Sense of Ability to Adapt Scale (GSAAS; (Front Psychol 14:985408, 2023)) at 4-month follow-up. Secondary outcomes are mental well-being, (parental) distress, and client satisfaction with “Adappt.”

**Discussion:**

Results of this study will contribute to knowledge on the effectiveness of a low-threshold application for parents of children with a NDD in multiple countries. If the application is found to be effective in improving mental health, recommendations will be made for implementation in health care.

**Trial registration:**

This study is registered on clinicaltrials.gov (NCT06248762) on February 8, 2024, and the Open Science Framework (https://osf.io/5znqv).

**Supplementary Information:**

The online version contains supplementary material available at 10.1186/s13063-024-08256-w.

## Introduction

The concept of neurodevelopmental disorders (NDDs) is based on criteria defined in the classification system of Diagnostic and Statistical Manual of Mental Disorders, Fifth edition (DSM-5) of the American Psychiatric Association. Whether NDDs are understood as disorder, disability, or just a difference between people depends on both context and culture. Where a health-care perspective is taken, the focus is on the impairments people with NDDs experience. NDDs are thought to be caused by an early disruption of the brain development with a negative impact on behavior, cognition, motor control, self-help and social communication [67]. Attention deficit hyperactivity disorder (ADHD), autism spectrum disorder (ASD), communication disorders (CDs), motor disorders (MDs) including tic disorders, intellectual disabilities (ID) and specific learning disabilities (SLDs) are classified under NDDs in the DSM-5TR [1]. Francés et al. [31] performed a systematic review on the prevalence of NDDs in children and found the prevalence rates ranging between 5 and 11% for ADHD, 0.7 and 3% for ASD, 1 and 3.4% for CDs, 0.8 and 17% for MDs, 0.6% for ID, and 3 and 10% for SLD.

NDDs not only affect the life of the persons or children with this condition, but may also have a profound impact on their families. Parents of children with ASD [9, 38], ADHD [71], or NDDs [18] have shown to experience more stress than parents of children with a typical development. A large body of research has been conducted on (causes of) stress in parents of children with NDDs, mainly in parents of children with ASD [24]. For example, NDDs are associated with a higher prevalence of sleep issues impacting the well-being of the family [5]. In addition, a significant association was found between parenting self-efficacy and well-being in mothers of children with ASD [51]. Furthermore, difficulties with understanding or dealing with the child’s behavior, struggles with support and care, and social stigma contribute to parental stress [9]. Taking care of a child with a NDD can also be challenging because the child’s needs change over time [10] and parents continuously face new challenges [22]. Therefore, being able to adapt to new challenges and changing situations is crucial for the mental health of these parents. Recently, a self-help application has shown to significantly improve the perceived ability to adapt in people with mild to moderate distress [73]. This shows the potential of improving the ability to adapt through digital interventions.

Although (early) interventions targeted at the child’s behavior or development can improve adaptive behavior of children with ASD [76] and ADHD symptoms in children with ADHD [16], these interventions did not have a significant effect on parenting stress [16]. Increased levels of parental stress are associated with a reduced family life dimension of parental quality of life [30], parental quality of life [56], health-related quality of life of children [15], and negatively influence the ability to raise the child (i.e., care and behavior management) [9]. This highlights the need to actively support the mental health of parents of children with a NDD.

A wide range of interventions have been developed to improve mental health of parents of children with NDDs, including mindfulness and positive psychology interventions (PPIs) [20, 22, 33, 53]. For instance, research suggests that parenting stress, anxiety, and depression can be improved through a diversity of interventions (e.g., mindfulness and PPIs) in parents of children with ASD [22]. Mindfulness training has also shown to be effective in reducing parenting stress in parents of children with ADHD [53, 70] and mothers of children with ASD [25]. Mindfulness is defined as being fully aware of cognitions, emotions, and experiences with a non-judgmental attitude from moment-to-moment [7, 44], and is supposed to improve emotion regulation [69]. This is especially relevant for parents of children with NDDs, since disturbances in emotion regulation of parents were found to correlate significantly with parental stress in parents of children with ASD [43]. PPIs are interventions that aim to promote positive behavior, cognitions, and feelings [64]. PPIs can consist of single interventions focusing on specific aspects such as gratitude, optimism, or meaning making. Combinations of interventions are called multicomponent PPIs (mPPIs) [40]. A recently performed large meta-analysis (*n* ≥ 72,000 participants) showed the effectiveness of PPIs for both clinical and non-clinical samples on various indicators of mental health [13]. Interventions consisting of multiple PPIs tended to have larger effects on mental health than single PPIs, and longer PPIs resulted in larger effects on mental health [13].

Traditional face-to-face (group-) interventions can have disadvantages that can cause additional stress, especially for parents of children with a NDD, such as availability restrictions, waitlists, and issues with arranging a babysitter [57, 72]. Therefore, flexible, low-threshold, and low-invasive supportive digital interventions for parents of children with a NDD seem to be a promising avenue to support their mental health. Digital interventions have the advantage of being broadly available and accessible without waitlists. In addition, research has shown that both mindfulness and PPIs can be successfully digitally delivered. Gál et al. [34] performed a meta-analysis of RCTs on mindfulness interventions delivered as digital application and found significant effects on anxiety, depression, perceived stress, and psychological well-being in diverse populations (e.g., students, clinical samples, general population). Furthermore, El Menshawy [26] performed a meta-analysis of online delivered PPIs (oPPIs) and found small but significant effects on well-being and depressive symptoms for adults. This indicates that digital interventions based on mindfulness and positive psychology can be used to improve mental health.

However, evidence on the effectiveness of interventions to improve mental health in parents of children with NDDs is scarce. Da Paz and Wallander [22] performed a review of these interventions especially for parents of children with ASD and concluded that available trials rarely focused on the long-term effects (i.e., > 3 months), sample sizes were generally small and generalizability is limited due to homogeneous samples (e.g., mainly mothers aged around 40). This indicates that there is a need for more robust research on interventions for this target group to support more definitive and generalizable conclusions. Furthermore, insight in core working mechanisms underlying the (potential) effects of PPIs on mental health-related outcomes for this target group is lacking.

Recently, researchers of the University of Twente developed a supportive self-help application (app) based on positive psychology and mindfulness, called “Adappt”, in cocreation with experts and parents. This app consists of evidence-based exercises based on the principles of positive psychology and mindfulness. The primary aim of the current intervention study is to examine the effectiveness of this intervention on the ability to adapt of parents of children with a NDD in an international randomized controlled trial with waitlist control condition. The secondary objectives are to evaluate (1) its effects on mental health including mental well-being, perceived stress, anxiety, depression, (2) its effects on parental experiences including parental self-efficacy, positive aspects of caregiving, (3) the role of core working mechanisms of the intervention including mindfulness, savoring, self-reassuring, psychological flexibility, and positive coping skills on the ability to adapt and mental health-related outcomes, and (4) users’ acceptance of and satisfaction with the intervention.

## Method

The Standard Protocol Items: Recommendations for Interventional Trials [14] guideline was followed to report this protocol. The study protocol and analysis plan were preregistered on the Open Science Framework (OSF, https://osf.io/5znqv) and the clinical trials register clinicaltrials.gov (NCT06248762).

### Study design

A non-blinded pragmatic international randomized controlled trial will be performed to study the effectiveness of Adappt in parents of children with a NDD. Participants will be recruited in France, Germany, Israel, Switzerland, and The Netherlands. However, participants from other countries that are able to understand one of the available languages (French, German, Hebrew, and Dutch) can sign-up for the study and participate if they meet the eligibility criteria.

After recruitment via service providers, parent associations, and social media (see “study procedure below”), interested parents fill in a screening form to check for eligibility. Eligible parents receive an e-mail with a link to the (online) baseline questionnaire (T0) and will then be randomized 1:1 to the experimental condition or waitlist control condition. Those randomized to the experimental condition start using the (unguided) digital intervention after the online baseline. One month after baseline participants will complete the post-measurement (T1). Furthermore, two follow-up measures will be conducted, at 4 months (T2) and 6 months after baseline (T3). Those randomized to the control condition receive the intervention that takes 1 month to complete after T2. The flow of participants and measurements can be found in Figs. 1 and 2.

**Fig. 1 Fig1:**
[figure not shown]
Flowchart of participants

**Fig. 2 Fig2:**
[figure not shown]
Procedure schedule. Note. * A more detailed overview of outcome measures and questionnaires can be found in Table 2. Adapted from Spirit (n.d.). Publications and Downloads. https://spirit-statement.org/publications-downloads/

### Participants

Eligible participants need to be (1) at least 18 years of age, (2) parent or primary caregiver of one or more children (younger than 18 years) diagnosed with or suspected of a NDD, (3) in possession of an e-mail address, (4) in possession of a smartphone or tablet with a stable internet connection that can be used to download and use the self-help app, and (5) willing to use the self-help app for a month, for approximately 10–15 min a day.

Since this self-help app intervention aims to support parents in reducing stress and promoting adaptive abilities, and is not a treatment for severe mental complaints, the following exclusion criteria are used: (1) being in treatment for a mental health issue, (2) presence of severe symptoms of anxiety as indicated by a score of at least 15 on the Generalized Anxiety Disorder (GAD-7; [66]), and (3) presence of moderately severe to severe symptoms of depression, as indicated by a score of at least 15 on the Patient Health Questionnaire (PHQ-9 [49],). Excluded participants will be informed about the reason for exclusion and those excluded for moderate to severe anxiety and/or depression levels will be advised to contact their local general practitioner.

### Study procedure

Participants will be recruited in the five countries (France, Germany, Israel, Switzerland, and The Netherlands), via (1) the social media channels of relevant stakeholders involved in the project, (2) associations for parents of children with NDDs, and (3) information leaflets and through health practitioners informing parents about the study in clinical centers for children with NDDs. Interested parents will be forwarded to a website of the study. At the website, the parent(s) will find more information about the study, the participant information letter, the option to ask questions via e-mail and have the option to register for the study. Therefore, participants will be referred to a Qualtrics questionnaire where they can register themselves and give informed consent, following the procedure of Kloos et al. [48]. Participants actively confirm that they (1) have read and understand the study information, (2) had time to consider participation and potential questions have been answered, (3) give consent for participation in the study, (4) know that participation is voluntary and withdrawal of consent can be done any time without giving a reason, and (5) consent to the use of their research data as described in the participant information letter.

Participants who give consent will be directed to the screening questionnaire, including questions related to in- and exclusion criteria (i.e., age of the participant, diagnosis, and age of the child with a NDD, being in possession of an e-mail address, smartphone/tablet, and stable internet connection, willingness to use the intervention, the PHQ-9, the GAD-7, and current treatment for a mental health issue). Recruitment will start in September 2024. It is expected that the required number of 212 participants (see “Sample size calculation”) will be reached in January 2025.

Eligible participants will receive a link to the online baseline questionnaire (T0) in Qualtrics, which takes about 30 min to complete. New T0-completers will be randomized once a week to the control or experimental condition and informed via e-mail about the allocation (see “Randomization and treatment allocation”). All participants allocated to the experimental condition will also receive the download instructions and can start using the intervention.

Parents will be invited to use the intervention daily for at least 30 days for 10–15 min a day. One month after baseline, all participants receive the post-intervention questionnaire (T1). The T1 measurement of the experimental condition will include additional questions to evaluate their satisfaction with and use of the intervention. It will take about 30 min (control condition) to 45 min (experimental condition) to complete T1. Four months after baseline, all participants receive the first follow-up questionnaire (T2), which takes about 30 min to complete. After the follow-up assessment control condition participants receive the download instructions and can use the intervention. Three months after the first follow-up questionnaire (7 months after baseline), all participants receive the second follow-up questionnaire (T3). The T2 of the control condition includes additional questions to evaluate the intervention and takes about 45 min to complete, whereas the questionnaire for the intervention condition takes about 30 min to complete. Participants that decided to withdraw from the study receive the opportunity to give feedback on the intervention and/or study.

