### Randomization and treatment allocation

T0-completers will be randomly assigned to the experimental or waitlist condition by the principal investigator using central block randomization, with a block size of 4. A priori created randomization schemes will be made using www.sealedenvelope.com. This tool provides random lists that will be combined with the participant IDs to randomly allocate participants to the experimental condition or waitlist control condition with an allocation ratio of 1:1.

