##### Parental experiences

Parental self-efficacy (16 items), behavioral (10 items), emotional (3 items), and total (16) problems of the child and prosocial behavior (8 items) of the child will be measured with the 24 item Child Adjustment and Parent Efficacy Scale – Developmental Disability (CAPES-DD; [27]). Parents rate their confidence in managing behavior of the child on a 10 point scale, ranging from “certain I cannot manage” (1) to “certain I can manage it” (10), resulting in a sum score between 16 and 160, with higher scores being indicative of higher parental self-efficacy levels. Child behavior items will be scored on a 4-point scale from not at all (0) to very much (3). Sum scores will be calculated for the subscales emotional problems (0–9), behavioral problems (0–30), prosocial behavior (0–24), and total problems (0–48). Psychometric properties were found to be very good [27].

Positive aspects of caregiving will be measured with the 9-item Positive Aspects of Caregiving (PAC; [68]). Items will be scored on a 5-point scale ranging from disagree a lot (1) to agree a lot (5). A sum score will be calculated (9–45), with higher scores being indicative of more positive aspects of caregiving. Psychometric properties were evaluated and found to be good [68].

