### Statistical methods

#### Sample size calculation

The required sample size was computed with RMASS2 software for two-group longitudinal designs with attrition [39]. Given a required power of 80% and a two-sided significance level of 5%, 106 participating parents will need to be recruited in each arm to detect a linear trend effect over the first three time points (a group by linear time interaction from T0 to T2) resulting in at least a moderate effect size difference between the groups (Cohen’s *d* = 0.5) at 4 months after baseline. So, at least 212 parents must be included in this RCT.

This sample size estimation is based on the assumption that the repeated measurements follow a first-order autoregressive (AR1) variance–covariance structure (starting at *ρ* = 0.5 between repeated measurements) and an assumed attrition of 10% between both the baseline (T0) and post-intervention (T1) and between the post-intervention (T1) and 4 month follow-up (T2) measurements. Given the relatively low number of involved countries (five) in the trial and the self-help nature of the intervention, no relevant clustering between participants at the country level is anticipated in the sample size calculation.

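### Nothing stated limits enrolment to one parent per child, and allocation is individual, so at least half of any co-enrolled couples would be split between app and waitlist; the effect on the primary outcome is probably small, and cheap to prevent

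*Protocol article*

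**What the plan says.** Participants (protocol article) defines eligibility person by person. The family criterion is being a "parent or primary caregiver of one or more children (younger than 18 years) diagnosed with or suspected of a NDD". None of the five inclusion or three exclusion criteria refers to another parent already in the trial. Study procedure leaves the number of parents open when it describes the study website: "At the website, the parent(s) will find more information about the study". The screening items listed under Study procedure do not ask about a co-parent either.

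Randomization and treatment allocation uses a 1:1 ratio and a block size of 4, with "random lists that will be combined with the participant IDs to randomly allocate participants". Household is neither the unit of allocation nor a stratum. Study procedure adds that new T0-completers are randomised weekly and told their arm by e-mail. Study design describes the trial as non-blinded.

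Waitlist control condition keeps the control arm off the app until the 4-month questionnaire (T2), which the Abstract names as the primary time point. Sample size calculation considers dependence between participants only at country level. Characteristics of parents and children records living with or without a partner, but not whether that partner is enrolled.

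**The concern.** Both parents of one child can each meet every listed criterion, and each would then receive a separate allocation. When the two allocations differ, a waitlist parent has a co-parent using the app during the period in which the control arm is meant to be unexposed.

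The activation code described under Data handling, management, and storage restricts who can log in. It does not stop partners from doing exercises together, or one partner from behaving differently toward the other. Table 1 includes themes on relationships and on asking for and accepting help, so some spill-over is credible.

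Two things are at stake. The app–waitlist difference in the GSAAS at T2 would be diluted. On the CAPES-DD child-behaviour items, parents in opposite arms could be scoring the same child. An analysis plan written later could describe split couples, but could not undo the split.

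**Working it through.** **1. The plan's own sample size.** From Sample size calculation: two-sided 5% significance, 80% power, d = 0.5 at T2 reached by a linear trend from T0, AR(1) correlation with ρ = 0.5, and 10% attrition at each of two steps (retention 1, 0.9, 0.81).

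The formula is n per arm = 2(z₀.₉₇₅ + z₀.₈₀)² · Var(c′y) / (c′δ)², with c = (−1, 0, 1) and δ = (0, 0.25, 0.5).

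- Var(c′y) = 1 + 1/0.81 − 2(0.25)/√0.81 = 1 + 1.2346 − 0.5556 = 1.679
- (c′δ)² = 0.25
- n = 2 × 7.849 × 1.679 / 0.25 = 105.4, rounded up to 106

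This matches the stated 106 per arm (212 in total). A generalised least squares version with monotone dropout gives 106.3. The figure is right on its own assumptions and has no reserve for dilution.

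**2. Probability that a couple is split.**

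- Different blocks: 1/2.
- Same block of 4 (two places per arm): once one partner is placed, 2 of the 3 remaining places are in the other arm, giving 2/3.
- Adjacent on the list: from 3 of the 4 block positions the next place is in the same block, so (3 × 2/3 + 1 × 1/2)/4 = 0.625.

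Weekly batches make it more likely that partners who register together sit close on the list. One half is therefore the lower end.

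**3. Dilution and power.** Let f be the share of participants in co-enrolled couples, p the probability of a split, and k the share of the effect that reaches the waitlist partner. The document gives neither f nor k; **both are assumptions**.

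- Share of waitlist parents exposed = f·p
- d* = 0.5(1 − f·p·k)
- Power = Φ(2.802 × d*/0.5 − 1.960)
- n per arm to restore 80% = 106 × (0.5/d*)², rounded up

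| f | p | k | Waitlist exposed | d* | Power | n per arm for 80% |
|---|---|---|---|---|---|---|
| 5% | 1/2 | 0.5 | 2.5% | 0.494 | 79.0% | 109 |
| 10% | 1/2 | 0.5 | 5.0% | 0.488 | 78.0% | 112 |
| 20% | 1/2 | 0.5 | 10.0% | 0.475 | 75.9% | 118 |
| 20% | 2/3 | 1 | 13.3% | 0.433 | 68.0% | 142 |

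In the first two rows, 106 × 0.025 = 2.7 and 106 × 0.05 = 5.3 waitlist parents are exposed. The last row sets all three quantities at the top of the range considered. The calculation covers dilution only and ignores correlation between partners' scores.

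**4. Which CAPES-DD scores are shared.** Under Parental experiences, "Parents rate their confidence in managing behavior of the child on a 10 point scale" describes the self-efficacy scale. That scale measures the parent's own confidence, so partners do not share the score. Only the child-behaviour items, scored 0 to 3, would be two ratings of one child.

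**The case against.** The strongest reply is that the premise rests on silence. The article never says that both parents may enrol, and the plural in the website sentence concerns people reading study information. A household rule could sit in the full protocol, the Open Science Framework registration or the information letter. This lowers confidence but does not remove the point, because the article lists its criteria and screening items and none imposes such a limit.

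The second reply concerns size, and most of it stands. The Discussion expects mostly mothers and reports that fathers were much harder to recruit, which points to few couples. Full spill-over would mean that living with a user is as good as one's own month of daily practice. The app is unguided and opened with a personal code, and some co-parents live apart.

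A reader might go further and infer that the control condition is substantially contaminated, that partners' child-behaviour scores overlap almost completely, or that nothing could be recovered later. The documents support none of these. They give no couple share or spill-over, and two parents need not rate a child alike. The child and family characteristics collected at screening and baseline might identify probable pairs for a sensitivity analysis, though imperfectly and without reversing the allocation.

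It is also fair to say that bias toward no effect would not create a false positive.

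**Conclusion.** The point holds as a design gap of probably small effect. As the article stands, both parents of a child can be enrolled and allocated separately, and between 1/2 and 2/3 of such couples would be split during the period when the waitlist should be app-free.

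The GSAAS is a parent's self-report, so the primary outcome is affected only through spill-over. With 5–10% of participants in co-enrolled couples and half spill-over, the cost is 1 to 2 points of power. The fall to about 68% needs 20% co-enrolment, every pair in one block and full spill-over together. Ratings of the same child from both arms concern only the secondary child-behaviour items. The sample size is not wrong on its own assumptions. Because the remedy is cheap and only works before allocation, the change should be made.

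**What to change.** Before recruitment, which Trial status gives as pending, add one screening question: is another parent or caregiver of the same child registering? Record a household ID. Then adopt one of two rules:

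- **One participant per household** is randomised, with the way of choosing that person fixed in advance.
- **Joint allocation**, only when both parents complete T0 before either is allocated: the pair is randomised as one unit and household enters the mixed model as a random effect.

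Under either rule, a parent who registers after the partner has been allocated should not be given the partner's arm as a randomised participant. Allocation is open and e-mailed weekly, so that parent would join knowing the arm, and partners of app users might join more readily than partners of waitlisted parents. This would break allocation concealment. Such parents should be left out of the randomised comparison.

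The cost is one screening item and one allocation rule. The first option loses a few second parents, mostly fathers, whose scarcity the Discussion already lists as a limitation. The second loses only late-registering partners, at the price of slight arm imbalance and a small loss of precision.
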